**2.- Purpose**

The purpose of the research is to determine whether, by controlling the patient's hemodilution level and, therefore, the acute anemia caused by the CPB priming fluid, continuous conventional ultrafiltration (CUF) can decrease serum lactate levels during normothermic CPB by increasing the hematocrit and, consequently, the supply of oxygen to the tissues, and whether the hemofiltration membrane can remove lactate molecules in situations of HL in CPB.

This will be done by performing arterial and venous blood gas analyses every 20 minutes during CPB to measure blood lactate levels, pH, oxygen delivery (DO2), oxygen consumption (VO2), oxygen extraction (ERO2), venous oxygen saturation (SvO2), arterial and venous carbon dioxide difference (△pCO2) and lactate levels in the effluent from the hemoconcentrator.

The perfusionist's role is essential during the procedure, as they control both Cardiac Output (CO) and gas exchange, as well as a number of variables that, depending on their action, will affect blood lactate levels.

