Correct cannulation of the patient before starting CPB, as well as the choice of the cardiopulmonary priming solution, allows us to perform the procedure safely, ensuring proper perfusion of the patient's organs and tissues.

Once CPB begins, the tissues are artificially perfused, for which the perfusion pump must be adjusted to a flow rate that is equal to the cardiac output of a healthy adult [3] (2.5 l/min/m2). This rate is adjusted throughout the CPB procedure to adapt to the patient's metabolic needs in order to ensure aerobic metabolism of the different organs and tissues, as the acute hemodilution caused by the priming liquid reduces the blood's oxygen content and blood viscosity, consequently causing hypotension.

Traditionally, during CPB, perfusionist nurses managed a series of gasometric, hematic and electrolyte values that, in theory, ensured safe extracorporeal perfusion, correcting them according to the flow of the CPB pump and temperature in order to maintain normal blood pH between 7.35 and 7.45, venous oxygen saturation (SvO2) >65 mmHg to ensure tissue perfusion, a hematocrit above 22% so as not to decrease the availability of oxygen in the blood, and blood glucose, calcium, sodium and potassium values within the normality.

HL can occur during or after CPB without clinical signs of hypoxia [4], increasing postoperative complications such as renal insufficiency (RI), neurological and respiratory changes and hemodynamic instability and causing acidosis. Consequently, patients require more time on mechanical ventilation, are hemodynamically unstable and more vulnerable to infections, all of which lengthens the patient's stay in the intensive care unit (ICU) and can lead to death [5].

Lactic acid is produced from pyruvic acid in a reaction catalyzed by lactate dehydrogenase and is rapidly buffered by the extracellular bicarbonate to produce lactate, normal serum values of which are lower than 2 mmol/L.

HL can begin according to organ involvement and is classified by whether it is related (type A) or unrelated (type B) to tissue hypoxia [6].

Type A HL is associated with CPB due to acute hemodilution and a deficient oxygen supply [7, 8] and is linked to patient morbidity and mortality in the postoperative period when lactate levels are above 4 mmol/L during the surgical procedure [9], as well as prolonging patients' stay in the Intensive Care Unit (ICU).

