MUF seeks to achieve more effective hemofiltration by hemoconcentrating the patient and reducing inflammatory mediators [12].

The surgical team at Puerta del Mar University Hospital who are taking part in the research usually use a polysulfone membrane throughout the procedure and perform high-flow continuous ultrafiltration (UF), replacing the filtered volume with Prismasol 2® pharmaceutical solution, which contains the following active substances: calcium chloride, dihydrate; magnesium chloride, hexahydrate; glucose monohydrate, lactic acid solution 90%; sodium chloride; potassium chloride and sodium hydrogen carbonate. This solution is also used for priming the CPB circuit, and it must be taken into account in the research that Prismasol 2® solution contains 3 mEq/L of lactate.

Prismasol 2® solution is used as a solution for hemofiltration in the treatment of renal insufficiency and no contraindications with CPB have been reported, since serum potassium and calcium levels are monitored every 20 minutes. The administration of sodium bicarbonate is also eliminated from priming.

Likewise, CUF during CPB is safe thanks to continuous patient monitoring throughout the procedure.

The flow rates recommended by the manufacturer for the replacement solution in hemofiltration and hemodiafiltration are as follows: Adults and adolescents: 500 - 3000 ml/hour.

The use of hemofiltration in adults during CPB procedures has evolved over the years, with studies showing the advantages of CUF or MUF in CPB procedures, such as increased hematocrit with the consequent reduction in blood transfusions, reduction of inflammatory response, improvement of hemodynamic parameters and better neurological outcomes in patients, as well as a shorter postoperative intubation time in the intensive care unit [13].

There is a disparity in the scientific literature regarding HL during and after CPB, and while Soliman R et al. [14] consider that continuous hemofiltration increases postoperative lactate levels and inotropic drug use, Kiziltepe et al. [15] describe it as a safe procedure in adult patients undergoing cardiac surgery.

Perhaps the results of the Soliman group were conditioned by the use of moderately hypothermic CPB and the use of Ringer's lactate solution at a concentration of 27.8 mEq/L for priming the CPB circuit.

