**4.4.- Specific objectives:**

- To determine plasma lactate levels in patients who undergo CPB at different stages of the process:
  - 10 minutes after starting CPB.
  - Every twenty minutes until the end of the CPB procedure
  - Twenty minutes after stopping CPB.
- To determine lactate levels in the effluent.
- To describe the behavior of variables that may influence intraoperative lactatemia levels.
- To evaluate the effects of using the polysulfone membrane continuously during the intraoperative and postoperative period.
- To describe the epidemiological profile, risk factors and surgical risk, according to the usual scores, of the patients in the study.
- To analyze the complications and side effects deriving from CPB and continuous hemofiltration with volume replacement.
- To identify patients' health status using the NANDA diagnosis classification.
- To assess patients' status of using the Nursing Outcomes Classification (NOC), before and after surgery with CPB.
- To evaluate the efficacy of the Nursing Interventions Classification (NIC), after CPB surgery using the Nursing Outcomes Classification (NOC).

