        - Haemoglobin in mg/dl and baseline haematocrit measured at the start of CPB (continuous quantitative viable). Use of blood products in priming and/or during the procedure, yes/no (dichotomous variable).
      - Additives:
        - Use of corticotherapy, yes/no (dichotomous variable).
        - Use of insulin, yes/no (dichotomous variable).
      - Times:
        - Surgery time, in minutes (continuous variable).
        - Aortic cross-clamping time in minutes (continuous variable).
        - Support time, in minutes (continuous variable).
        - Haemofiltration time, in minutes (continuous variable).
        - Time from unclamping to patient decannulation, in minutes (continuous variable).
      - Haemofiltration:
        - Duration, in minutes (continuous variable).
        - Total volume (VTot) extracted in the effluent and Replacement volume (VolR) with plasma solution during CPB, in thousands (continuous variable).
        - Water balance during CPB (VTot-VolR), in millimeters (continuous variable).
      - Metabolic and homeostatic control:
        - Blood gas, acidosis yes/no (dichotomous variable).
        - Glucose, in mg/dl (continuous variable).
        - Temperature, in degrees centigrade (continuous variable).
        - Anion gap in mEq/L (in order to diagnose potential lactic acidosis in cases of poorly-defined metabolic acidosis with levels above 12 mEq/L) [22] (continuous variable).
  - Surgical variables:
    - Surgical procedure performed.
      - Valve surgery, yes/no (dichotomous variable).
      - Coronary surgery, yes/no (dichotomous variable).
      - Combined surgery, yes/no (dichotomous variable).
  - Postoperative variables in ICU.
    - Clinical and scale variables:
      - Intubation time, in hours. (continuous variable).
      - Time of stay in ICU, in hours. (continuous variable).
      - Number of hours on inotropic and/or vasoactive support. (continuous variable).
      - Blood loss.
        - Transfusion of blood products, yes/no (dichotomous variable).
        - Postoperative hospital stay, in days (quantitative variable).
        - Hospital mortality, death yes/no (dichotomous variable).

Hematocrit in percentage (continuous variable).

SOFA score [23] (Annex II) (categorical variable).

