**5.6.- Sample size**

The sample size will result from the prospective inclusion of a consecutive series of patients over 10 months who undergo surgery with CPB by the investigator in the Cardiovascular Surgery Unit of Puerta del Mar University Hospital, Cádiz, under normothermic conditions. As a preliminary analysis, this cohort is estimated to consist of about 40 patients in the Cardiovascular Surgery Unit.

The study population will comprise a sample of patients who meet the inclusion criteria between February 2017 and December 2017.

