**5.7.- Statistical analysis [24]:**

- Descriptive analysis of variables: measures of central tendency and dispersion will be shown in the case of quantitative variables, while frequencies and proportions will be shown in the case of categorical variables.
- The normality of the variables will be checked using graphs and the Kolmogorov-Smirnov test.
- Homogeneity and comparability between the groups of the two arms of the study in the main confounding factors considered will be verified at the beginning of the study by means of a comparison of proportions (chi-squared test or Fisher's exact test, if necessary) and a comparison of means (Student's t-test and the Mann-Whitney U test in case of non-parametric distributions).
- The intrasubject change over time will be analyzed by comparing paired means using a t-test or Wilcoxon signed rank test (non-parametric variables), quantifying the change in each measure in relation to the baseline reference measure (first sample).
- The bivariate analysis between the CG and PG will be performed using the chi-squared test or Fisher's exact test, if necessary, and using a comparison of means (Student's t-test and Mann-Whitney U test in case of non-parametric distributions).
- In the event of non-homogeneity in any variable between the groups studied, a multivariate analysis will be performed using linear regression.

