**5.8.- Limitations of the study and ethical considerations**

The study design does not allow the use of total blinding, and the perfusionist is aware of the therapy and characteristics of the membrane at all times. According to the literature and standard practice in this country, the use of a control group should not pose any ethical dilemma if certain premises are taken into account.

The only condition that the control group must meet is that the patients must be able to manage their fluid balance by themselves, as a fluid overload has been shown to be harmful. This may mean that the patients in the control group have better renal function than those in the other group, or at least better initial diuresis. However, the primary objective is not to measure or evaluate perioperative renal function. In addition, a hemofilter will be available for use if control patients are not able to manage their fluid balance through diuresis. Finally, if surgery times are shorter in the control group, the lactatemia levels may be lower than in the other group with a longer duration. If this is the case, we will stratify the treatment groups by selecting cases with a shorter duration. In any case, a minimum time of 60 minutes is established from start of CPB + CUF and to the end of CPB.

It will be carried out according to the international ethical recommendations (the Declaration of Helsinki and the Oviedo Convention), since the use of the best available therapy according to the patients' circumstances is contemplated at all times.

In order to safeguard confidentiality, all personal data collected as part of this study will be treated in accordance with Organic Law 15/1999, of December 13, on personal data protection.

Likewise, informed consent will be requested for surgery that includes the usual CPB procedures with or without hemofiltration.

Informed consent will also be requested for use of any data deriving from medical records and analytical determinations. Access to personal information will be restricted to the investigator and authorized personnel and all of them will be obliged to maintain confidentiality. If the work is published, the patients' identity will remain anonymous at all times.

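### Section 5.4 reduces blood gas to an acidosis flag although pH is measured as a number every 20 minutes: alkalosis is read as normal, and a general pH shift is harder to detect

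*Protocol*

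**What the plan says.** Section 5.4, under metabolic and homeostatic control, lists "Blood gas, acidosis yes/no (dichotomous variable". No cut-off or time point accompanies it. Glucose, temperature and anion gap in the same block are continuous. Numeric pH does not appear in the section 5.4 list.

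Section 2 plans "arterial and venous blood gas analyses every 20 minutes during CPB to measure blood lactate levels, pH" among other quantities, so pH exists as a repeated number. Section 3 describes the perfusionist's aim as to "maintain normal blood pH between 7.35 and 7.45", a range with an upper and a lower limit.

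Section 5.7 ties the between-arm test to the scale of the variable: "The bivariate analysis between the CG and PG will be performed using the chi-squared test or" Fisher's exact test for categorical items, and Student's t-test or Mann-Whitney for numeric ones. The nearest objective, in section 4.4, is "To describe the behavior of variables that may influence intraoperative lactatemia levels". On size, section 5.6 says "this cohort is estimated to consist of about 40 patients".

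**The concern.** A number measured several times per patient is listed as one yes/no item, and the item looks in one direction only. Two consequences follow if it is used as listed.

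First, a patient whose pH rises above 7.45 and never falls below the acidosis limit is coded the same as a patient with normal pH. The direction of any pH effect is open here. The replacement fluid described in section 3 contains lactic acid as well as "sodium chloride; potassium chloride and sodium hydrogen carbonate", and it replaces the volume removed by the filter.

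Second, cutting a number in two discards information about its size. With about 40 patients there is little precision to give away. What is at stake is the description and comparison of pH, one of the variables that may bear on lactate. The lactate results themselves are not at stake.

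**Working it through.** **No figure in the plan to reproduce.** Section 5.6 gives a recruitment estimate without power, effect size or SD. The one arithmetic check is section 5.1's eight blocks of five, 8 × 5 = 40, which agrees with section 5.6. The allocation ratio is not stated. Everything below assumes 20 per arm and a two-sided 5% level. Acidosis rates, SDs and shifts are also assumptions, because the protocol gives none.

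**Step 1. Alkalosis.** This follows from the coding. With acidosis meaning a low pH, 7.40 and 7.50 are both coded no, whatever cut-off is chosen. A simulated example (4,000 runs) has 10% of patients acidotic in both arms, the rest centred at 7.40 in controls and 7.46 in the filter arm, SD 0.02. Power is 96% for the t-test, over 99% for Mann-Whitney and about 1% for Fisher on the flag.

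**Step 2. A general shift.** Let per-patient pH be normal with equal SD, shifted by d SD between arms.

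- t-test: noncentral t with 38 degrees of freedom and noncentrality d × √(20/2). Power of 80% requires d = 0.909. Mann-Whitney at that shift has about 78%.
- Flag: if a share p of controls is acidotic, the filter-arm share is Φ(Φ⁻¹(p) − d) when pH moves up and Φ(Φ⁻¹(p) + d) when it moves down. Power comes from enumerating all 2×2 tables, with Fisher when an expected count is below 5 and uncorrected chi-squared otherwise.
- Relative loss = (0.80 − power)/0.80.

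| Control acidosis | Filter arm, pH up | Power (loss) | Filter arm, pH down | Power (loss) |
|---|---|---|---|---|
| 20% | 4.0% | 0.201 (75%) | 52.7% | 0.594 (26%) |
| 30% | 7.6% | 0.367 (54%) | 65.0% | 0.588 (26%) |
| 40% | 12.3% | 0.510 (36%) | 74.4% | 0.592 (26%) |
| 50% | 18.2% | 0.588 (26%) | 81.8% | 0.588 (26%) |

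Across t-test powers of 50% to 90% and control rates of 10% to 50%, the loss under this model runs from 20% to 96%. For small shifts, the efficiency of the flag relative to numeric pH is φ(c)²/[p(1 − p)], with c = Φ⁻¹(p). That is 0.64 at p = 0.5, 0.49 at 0.2 and 0.34 at 0.1.

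**Step 3. Where the loss disappears.**

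- *Effect confined to an acidotic subgroup.* Take 40% against 5% of patients centred at 7.32 and the rest at 7.40, SD 0.03. Power is 54% (t-test), 44% (Mann-Whitney) and 46% (Fisher on the flag), so they are similar.
- *Brief dips that are corrected.* Take five samples per patient, mean 7.41, between- and within-patient SD 0.02, and a one-sample dip of 0.10 in 50% against 10% of patients. Averaging over five samples shrinks the dip to 0.10/5 = 0.02, so mean pH differs by only (0.50 − 0.10) × 0.02 = 0.008 between arms. Over 3,000 runs, mean pH has power 19% (t-test) and 18% (Mann-Whitney). A flag for any pH below 7.35 has 55% (Fisher) or 67% (Fisher or chi-squared by expected count). With a dip of 0.08 the four figures are 14%, 14%, 40% and 51%.

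**The case against.** The strongest reply is that an event flag suits a managed quantity. Section 3 says perfusionists correct pH towards its range, so excursions may be short. A per-patient mean dilutes them, and a flag for any acidosis keeps them. The second case in step 3 bears this out. It stands, and it rules out replacing the flag with mean pH alone. A reader might infer that a yes/no code always costs power. The documents do not support that, because they do not say what form a pH effect would take.

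The flag also has a clinical use. Section 5.4 pairs it with a continuous anion gap to help identify lactic acidosis, and no hypothesis or objective concerns alkalosis. That is a good reason to keep the flag. It does not make the flag an adequate description of pH, which section 4.4 calls for if pH is among the variables that influence lactate.

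A reader might also infer that numeric pH will be lost. Section 5.4 is not exhaustive: it also omits oxygen delivery, consumption and extraction, venous saturation and the CO₂ difference, all of which section 2 plans to measure. Numeric pH is probably on the record sheets, and a statistical analysis plan that is not shown may use it. The point is therefore limited to the scale that section 5.4 states, used as stated.

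Finally, power is a modest yardstick for an item with no hypothesis of its own. That is accepted, and it sets the severity.

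**Conclusion.** The point holds as a minor one. Used as section 5.4 states it, the blood gas item cannot separate alkalosis from normal pH. This follows from the coding and needs no assumed figure. For a general shift in pH the item is also less powerful than the number already measured: 20% to 59% against 80% in the main illustration. Those figures rest on 20 per arm, normal per-patient pH and assumed acidosis rates and shifts, so they illustrate the effect and are not properties of the plan. The power loss is conditional, as step 3 shows.

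It would be wrong to carry the point over to the trial's main conclusion. Lactate is a separate continuous variable and its analysis is unaffected. Any pH result, on either scale, describes pH under management, since section 5.8 states that "the perfusionist is aware of the therapy and characteristics of the membrane at all times". It should be read as supporting and descriptive.

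**What to change.** In section 5.4, replace the single blood gas line with three entries:

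- acidosis: any arterial pH below 7.35 during bypass, yes/no;
- alkalosis: any arterial pH above 7.45 during bypass, yes/no;
- arterial pH at each blood gas sample, continuous.

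Compare per-patient mean arterial pH between arms with the t-test or Mann-Whitney test of section 5.7, and report it alongside both flags. Present all three as supporting results on pH under management by an unblinded perfusionist. Keeping the defined flags beside the number avoids having to guess whether an effect would be a general shift or a set of short episodes.

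The cost is a few lines of text, slightly more data entry and a short extra analysis of values the blood gas already yields. Samples, objectives and the lactate analysis do not change.

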We will also analyze the possible beneficial effects of optimal therapy on clinical progress in the ICU in the form of reduced need for blood transfusion, mechanical ventilation for less than 24 hours, reduced need for extracorporeal renal support, reduced need for vasoactive drugs, shorter stay in the ICU, shorter hospital stay and reduced mortality. This analysis will enable us to collect information that will allow subsequent patient follow-up in terms of morbidity and mortality.

Finally, based on the important role of perfusion nursing care in patients undergoing cardiac surgery with CPB, and in view of the lack of scientific production in this respect, we propose to assess patients who undergo CPB by means of NANDA, NIC and NOC nursing terms before and after surgery. There are other taxonomies, but these are the most widely accepted and will be used as follows:

- NANDA diagnosis (North American Nursing Diagnosis Association).
- NOC (Nursing Outcomes Classification) of the patient’s current situation and the outcome we hope to achieve.
- NIC (Nursing Interventions Classification).
- NOC that we have achieved.

The interrelationship between these three taxonomies [17] describes the actual or potential problem that we have detected in the patient and the aspects of that problem that we are attempting or hope to solve with one or more nursing interventions, in which one or more activities needed to solve the problem will also be used.

Diagnoses:

- NANDA Code 0027: “Fluid Volume Deficit”
  - Definition: Decreased intravascular, interstitial and/or intracellular fluid. This refers to dehydration, water alone without changes in sodium.
    - NOC Code 0601:
      - Definition: “Water balance in the intracellular and extracellular compartments of the body”.
        - NIC 4120 “Fluid management”: Promotion of fluid balance and prevention of complications resulting from abnormal or undesired fluid levels.
        - NIC Code 4130: “Fluid Monitoring”: Collection and analysis of patient data to regulate fluid balance.
        - NIC Code 7690: “Laboratory data interpretation”: Critical analysis of patient laboratory data in order to assist with clinical decision making.
        - NIC Code 4180: “Expansion of intravascular fluid volume in a patient who is volume depleted”
- NANDA Code 00016: “Impaired urinary elimination”
  - Definition: Impaired urinary elimination.
    - NOC Code 0503:
      - Definition: “Collection and discharge of urine”.

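### Intubation, ICU, vasoactive-support and hospital times are compared as raw durations with shorter read as better, so a death that cuts a duration short can count as a favourable value

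*Protocol*

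**What the plan says.** Protocol section 5.4, under the postoperative ICU variables, defines four durations as plain quantities: "Intubation time, in hours. (continuous variable"), "Time of stay in ICU, in hours. (continuous variable"), "Number of hours on inotropic and/or vasoactive support. (continuous variable") and "Postoperative hospital stay, in days (quantitative variable"). Death appears in the same list as its own item, "Hospital mortality, death yes/no (dichotomous variable"), with no link to the durations.

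Section 5.7 says the two arms will be compared "using a comparison of means (Student's t-test and Mann-Whitney U test in case of non-parametric distributions").

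Section 3 gives the direction. Among the hoped-for benefits it names "mechanical ventilation for less than 24 hours" and "shorter stay in the ICU, shorter hospital stay and reduced mortality". Section 4.2 then hypothesises that hemofiltration lowers both morbidity and mortality.

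No section says how a patient who dies enters any of the four durations.

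**The concern.** Each duration has a natural end: extubation, weaning from support, ICU discharge or hospital discharge. If the patient dies first, the recorded time stops at death and says nothing about recovery. Where shorter means better, an early truncated time is credited as a good result. For example, a patient who dies on the ventilator 10 hours after surgery would have 10 intubation hours and would meet the under-24-hour criterion.

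The protocol's own rationale in section 3 puts long stay and death on the same pathway from hyperlactatemia. If hemofiltration prevented early deaths, the raw durations would penalise the arm that did better. If it caused them, the durations would flatter the arm that did worse. At stake is the morbidity half of the second hypothesis in section 4.2.

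**Working it through.** **Inputs from the protocol.** About 40 patients (section 5.6); eight blocks of five (section 5.1), 8 × 5 = 40, which agrees. The variables, test and direction are as set out above. The protocol gives no power calculation, mortality rate or distribution of stays, so there is no planned figure to reproduce.

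**Assumptions.** 20 per arm (the allocation ratio is not stated); hospital mortality of 2 to 5%; for the illustration, survivors' ICU stay lognormal with median 60 h and log-SD 0.6. PG is the hemofiltration arm, CG the control arm.

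**1. Largest effect of one death on the rank test.** There are 20 × 20 = 400 between-arm pairs. Moving one patient from the shortest to the longest rank changes U by at most 20, that is 20/400 = 0.05 in the probability that a PG stay is shorter than a CG stay.

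- SD(U) under the null = √(20 × 20 × 41 / 12) = 36.97.
- One death: 20 / 36.97 = 0.54 in z. Two in the same arm: 40 / 36.97 = 1.08.
- If the split were 16:24, SD(U) = √(16 × 24 × 41 / 12) = 36.22, and the bound per death is 16/36.22 = 0.44 or 24/36.22 = 0.66, depending on the arm.

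These are upper bounds: they require the patient who dies to hold the very shortest recorded value.

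**2. How likely any death is.** Among 40 patients, P(at least one) = 1 − 0.98^40 = 0.55 at 2% mortality and 1 − 0.95^40 = 0.87 at 5%. This counts hospital deaths at any time, not only early ones.

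**3. Can the sign change?** Take 20 evenly spaced lognormal quantiles per arm, with PG stays truly 10% or 20% shorter. Let the CG patients who would have stayed longest die at 12 h instead.

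| True PG effect | CG deaths at 12 h | Mean difference, PG − CG | P(PG shorter), raw | P(PG shorter), deaths ranked worst |
|---|---|---|---|---|
| 10% shorter | 0 | −7.1 h | 0.552 | 0.552 |
| 10% shorter | 1 | +2.0 h | 0.502 | 0.552 |
| 10% shorter | 2 | +8.6 h | 0.455 | 0.555 |
| 20% shorter | 0 | −14.2 h | 0.598 | 0.598 |
| 20% shorter | 1 | −5.1 h | 0.548 | 0.598 |
| 20% shorter | 2 | +1.5 h | 0.500 | 0.600 |

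For a 10% effect, one death reverses the mean difference and wipes out the rank difference; two reverse both. For a 20% effect, two deaths reverse the mean difference but only cancel the rank difference.

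The example is deliberately unfavourable. The longest CG stay is 60 × exp(0.6 × 1.96) = 194.5 h, so that death moves the CG mean by (194.5 − 12)/20 = 9.1 h. If the patient who died would have had a stay of about the median, 60 h, the move is (60 − 12)/20 = 2.4 h, and −7.1 h becomes −4.7 h with no reversal.

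**4. On average over simulated trials** (same stays, deaths at 2 to 24 h, P(PG shorter)):

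- Equal mortality of 2%, equal survivor stays: 0.498 raw, 0.499 with deaths ranked worst.
- Equal mortality of 3%, PG stays 15% shorter: 0.571 raw, 0.570 ranked worst.
- Mortality 10% in CG and 0% in PG, equal survivor stays: 0.454 raw, 0.552 ranked worst.

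The average moves only when deaths are unequal. In a single trial with equal underlying mortality of 2 to 3%, the sign of the rank comparison still differed between the two methods in about 12 to 13% of runs, because chance alone can put an early death in one arm.

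**The case against.** The strongest reply is that handling of deaths in secondary outcomes is commonly left to a statistical analysis plan, which may exist. The protocol never states that the durations end at death. The four durations are also absent from the dependent variables listed in section 5.4, and the 24-hour criterion appears only in the background. Mortality is a dependent variable, so an imbalance would be seen. Emergency surgery is excluded, so deaths may be few.

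Much of this stands, and it limits the size of the point. It does not remove it: the protocol itself has fixed the form of the variables, the test and the favourable direction, and together these credit an early death. Reporting mortality separately makes the problem visible but does not correct the ranks.

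A reader might go further and infer that the worst outcome is scored as the best on all four measures. The documents do not support that. All four durations stop at death only if the patient dies in the ICU, still intubated and still on support. Vasoactive hours can be zero, so a patient who dies on support can rank worse than survivors who needed none. A patient extubated and weaned early who dies later on the ward has valid intubation and support times. Deaths after a long stay carry long durations already.

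**Conclusion.** The point holds in a limited form. As written, the comparison can count a death that cuts a duration short as a favourable value, and with about 20 per arm (assumed) one or two excess early deaths in one arm could mask or reverse a modest difference. The shift in z is at most about 0.54 per death.

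It should not be read as a systematic bias: with equal mortality there is none on average. Nor is 55 to 87% the chance of distortion; it is the chance of any hospital death at an assumed 2 to 5% mortality, and only early deaths do the harm. The reversals shown depend on the assumed stay distribution and on the patients who died being those who would have stayed longest. The outcomes are secondary to intraoperative lactate. The change is worth making because it is cheap, but the main comparison does not depend on it.

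**What to change.** Add a rule for these four durations to section 5.7:

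- For each duration, give the worst rank, above the longest survivor value, only to patients who die before that duration has ended: before extubation for intubation time, before weaning for vasoactive-support time, before ICU discharge for ICU stay, before hospital discharge for hospital stay. Patients whose duration ended before death keep the recorded value.
- Compare the arms by Mann-Whitney for these four variables.
- Count a death before extubation as not meeting the under-24-hour ventilation criterion.
- Report deaths by arm beside each duration, and show durations in survivors as description only.

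Applying the rule duration by duration matters. A blanket worst rank on all four for every in-hospital death would mis-score the patient who recovered from ventilation and support and died later on the ward.

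The cost is a few sentences. Death is already recorded, and whether it came before each endpoint should be available from the ICU and ward records that section 5.4 names as sources. The t-test option is given up for these variables, so the result is a rank comparison and not a mean difference in hours. A patient who dies on full support will count against the arm in all four durations as well as in mortality, and the report should say so.
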